#### Physical activity

2.1.5

Physical activity was monitored using two different accelerometers. To assess physical activity patterns during the dietary intervention, physical activity was continuously monitored using the ActiGraph wGT3X/wGT3X-BT (ActiGraph, Pensacola, United States). The accelerometer was worn on the hip and the device was only removed during sleeping and bathing.

To measure light physical activity and time spent sedentary or standing, the ActivPAL3 micro (PAL Technologies, Glasgow, Scotland) was used for three non-consecutive weeks during the dietary intervention in addition to the ActiGraph. The ActivPAL was also used to examine the association between habitual sleep patterns and postprandial glucose responses. The ActivPAL was wrapped in a waterproof sleeve and attached to the right anterior thigh to ensure continuous data collection during day and night. Data were extracted after one week using PAL Software Suite version 7 (PAL Technologies, Glasgow, Scotland). During the wear-time of the ActivPAL, participants recorded sleep- and wake times in an online diary.

#### Time-restricted eating test

2.1.6

Glucose metabolism has a diurnal pattern (21). Consumption of food products in the evening is associated with a higher glucose response compared to consumption in the morning (22). To examine the relationship between time of eating and postprandial glucose responses, participants underwent two days of time-restricted eating. On three Saturdays in the dietary intervention, the exact same meals were consumed during a different time window. On one Saturday, the standardized diet was consumed between 07:00–15:00, on a second Saturday between 14:00–23:00, and on a third Saturday, participants followed their regular schedule. The shift in the restricted time window for eating enables examination of the effect of eating time on postprandial glucose responses. Furthermore, we aimed to assess the relation between the glucose variability during the different time windows with the chronotype of an individual, i.e., whether the participants indicate themselves as a morning-type or an evening-type, using the reduced Morningness-Eveningness Questionnaire (rMEQ) (23).

### Measurements

2.2

Before the start of the dietary intervention, the baseline parameters of the participants were comprehensively characterized during three non-consecutive clinical test days (Figure 2). During these days several measurements were performed, including an MRI/MRS, an oral glucose tolerance test (OGTT), and a high-fat mixed meal (HFMM) challenge test. To prevent an effect of the order of the OGTT and the HFMM, the clinical test days were separated by at least one week. Glucose was continuously monitored during the OGTT and the HFMM and the six days at home in between the two tests. In addition to the characterization period, several measurements were performed during and after the intervention. An overview of all measurements performed during the RepEAT study is described in Table 1.

**Figure 2 fig2:**
[figure not shown]
Overview of the characterization period. The characterization period consisted of three non-consecutive clinical test days and the collection of samples at home, spread over a total of three weeks. To prevent an effect of the order of the OGTT and the HFMM, the clinical test days were separated by at least one week. After a standardized meal, the evening before test days 2 and 3, participants remained fasted until arrival at the research facility. Glucose monitoring started at least 2 days before the start of test day 2. Note that the order of test days is an example, test day 2 and 3 were reversed for half of the study population. The MRI/^1^H-MRS was planned after test day 2 and 3 for some participants. CANTAB, Cambridge Neuropsychological Test Automated Battery; HFMM, high-fat mixed meal; MRI, magnetic resonance imaging; ^1^H-MRS, proton magnetic resonance spectroscopy; OGTT, oral glucose tolerance test.

**Table 1 tab1:** Overview of measurements during the RepEAT study.

Outcome category	Method	Main parameters	Week		
			0	0–9	9
Anthropometrics, body composition	Weighing scale	Body weight	●	●	●
	Measuring tape	Height, waist, and hip circumference	●		
	Magnetic resonance imaging (MRI)	Abdominal subcutaneous adipose tissue, visceral adipose tissue	●		
	Proton magnetic resonance spectroscopy (^1^H-MRS)	Intrahepatic lipid content	●		
Laboratory fasting and challenge tests	Fasting blood collection	Fasting glucose and lipid metabolism	●		●
	Oral glucose tolerance test	Glucose homeostasis parameters	●		
	High-fat mixed meal	Fasting and postprandial metabolic profile	●		
Measurements in daily life	Continuous interstitial glucose concentrations	Postprandial glucose responses, glycaemic variability	●	●	
	Physical activity monitoring	ActiGraph (9 weeks), ActivPAL (3× 1 week)		●	
Microbiota composition and functionality	Faeces collection	Faecal microbiota composition	●	●	●
	Bristol stool chart	Stool frequency and consistency	●	●	●
	Blue dye method	Transit time	●		●
	Saliva collection	Oral microbiota composition	●	●	●
Immune function	SCENITH*	PBMC metabolic profile**	●		●
	Transcriptomics	PBMC transcriptome	●		●
Cognitive performance	Cambridge Neuropsychological Test Automated Battery	Attention & psychomotor speed, memory, executive function	●		
Genetics	Buccal swab/buffy coat collection	Genetic variation in genes relevant to metabolism and response to food	●		●
Amylase	Saliva collection	Amylase concentration	●	●	●
Questionnaires	General questionnaire	Demographics, medication use, lifestyle	●		
	Food frequency questionnaire	Habitual dietary intake	●		
	Perceived stress scale-10	Perceived stress	●		
	Reduced morningness-eveningness questionnaire	Chronotype	●		
	Pittsburg Sleep Quality Index	Sleep quality	●		
	Multidimensional Mood Questionnaire	Self-reported mood		●	

*SCENITH: Single Cell Energetic metabolism by profiling Translation inhibition. **PBMC: peripheral blood mononuclear cells.

#### Anthropometry

2.2.1

The body weight of participants was measured using a calibrated digital scale to the nearest 0.1 kg. Height was measured using a telescopic measuring tape to the nearest 0.1 cm. Participants did not wear shoes or heavy clothes during both measurements. Waist and hip circumference were measured in duplicate to the nearest 0.1 cm.

#### OGTT and HFMM

2.2.2

To characterize the metabolic response to a meal challenge and to determine insulin resistance, a 7-point oral glucose tolerance test (OGTT) and a high-fat mixed meal (HFMM) test were performed once per individual in the characterization period. The evening before both the OGTT and the HFMM, participants consumed a standardized dinner (24% of energy intake (en%) fat, 54 en% carbohydrates, 22 en% protein; in total 2,380 kJ/565 kcal). After the standardized dinner participants remained fasted until arriving at the research facility. In addition, participants refrained from heavy exercise the evening before and the morning of these tests. Thirty minutes before the start of the test, a venous catheter was placed.

For the OGTT, at *t* = 0 min, participants drank 200 mL of a 75 g glucose solution (Glucomedics, Breda, The Netherlands) within five minutes. Blood was collected in the fasted state before (*t* = 0), and 15, 30, 45, 60, 90, and 120 min after consumption of the glucose solution, to measure plasma glucose and insulin concentrations. The HFMM was provided in the form of a shake and consisted of 320 g water, 20 g protifar, 83.5 g dextrose, 60 g palm olein, and 20 drops of vanilla oil. In total, the shake contained 3,833 kJ and 76.3 g carbohydrates, 17.6 g protein, and 60 g fat (24). To make sure there was no difference in metabolic response due to a difference in consumption speed, participants were instructed to consume the drink in 10 min. Blood samples were collected before consumption (*t* = 0) and 30, 60, 90, 120, 180, and 240 min after the consumption of the HFMM for the measurement of plasma glucose and insulin, free fatty acids, short-chain fatty acids, triglycerides, cholesterol, gut hormones, metabolomics, and proteomics including cytokines. At each time point, the first 2 mL of blood was discarded before drawing the blood samples because it could still contain the physiological salt of the venflon line.

#### Fasting blood outcomes

2.2.3

Fasting blood samples were collected at baseline, before the start of the OGTT or HFMM, and at the end of the 9-week dietary intervention. Fasting blood was collected to measure glucose homeostasis, oxidative stress markers, plasma concentrations of advanced glycation end-products (AGEs), and immune cell metabolism. We aimed to determine fasting glucose homeostasis by measuring plasma glucose, insulin, and glycated haemoglobin (HbA1c) concentrations after an overnight fast. In addition, fasting blood samples were collected to measure concentrations of oxidative stress markers, and to determine the plasma concentrations of α-dicarbonyls and advanced glycation end-products (AGEs) using ultraperformance liquid chromatography–tandem mass spectrometry. Furthermore, fasting blood samples were used to isolate peripheral blood mononuclear cells (PBMCs) and perform immune cell metabolic profiling using an adapted version of SCENITH (Single Cell Energetic metabolism by profiling Translation inhibition) (25). Additionally, peripheral blood mononuclear cells were stored in Trizol for transcriptomic analysis.

#### 24-h urine

2.2.4

Before and at the end of the 9-week dietary intervention, 24-h urine was collected to measure oxidative stress markers. Participants collected 24-h urine in 3 L containers at home. The measurement started after the first voiding in the morning and ended 24 h later. At the day of urine collection, participants ingested a tablet containing 100 mg of para-aminobenzoic acid (PABA) during during breakfast, lunch, and dinner, to check whether all urine was collected. Participants were asked to store the urine samples in a cool place until turning them in the next day. Urine samples per participant were mixed, the volume was measured, and aliquots were stored at −80°C until further analysis.

#### Skin autofluorescence

2.2.5

Next to the plasma concentrations of AGEs, the accumulation of AGEs in the skin was measured by skin autofluorescence at 440 nm using an AGE reader (Diagnoptics, Groningen, Netherlands) (26). This is a non-invasive procedure in which the participants rested their lower arm on the AGE reader for 12 s during which the skin autofluorescence was measured. Participants were instructed to not apply any body cream or sunscreen on the day of the measurement. The measurement was performed on a skin site without skin abnormalities such as scars, tattoos, or birthmarks.

#### Magnetic resonance imaging/spectroscopy

2.2.6

Magnetic resonance imaging (MRI) was used to measure abdominal fat distribution and to guide spectroscopic measurements for quantification of intrahepatic lipid (IHL) content. The procedures were performed on a Philips Ingenia Elition 3 T X MRI scanner (Royal Philips, Amsterdam, Netherlands). Participants were asked to refrain from eating and drinking two hours before the start of the scan to ensure that digestion did not interfere with the measurements. The scans were performed in the MRI/MRS-scanner using a body coil with the participant in a supine and head-first position. Breath-hold techniques on exhalation were used to avoid breathing-induced artefacts.

To measure abdominal fat distribution, axial T1-weighted spin echo images were acquired and slices were centred at the interspace L3-L4. Visceral (VAT) and subcutaneous adipose tissue (SAT) and their ratio were quantified using the software Slice-O-Matic version 6 Rev-7. To quantify the intrahepatic lipid (IHL) content, proton magnetic resonance spectroscopy (^1^H-MRS) was used. Fine shimming was performed to optimize the magnetic field homogeneity within the region of interest and a 30x30x20 mm voxel was placed in the upper right liver lobe. Vascular structures and the proximity of subcutaneous fat were avoided during the voxel placement. The water signal in the ^1^H-MRS spectra was suppressed using frequency-selective pre-pulses and the spectra were fitted to quantify the lipid peak. Liver measurements were triggered 500 ms following inhalation. The ^1^H-MRS spectra were processed and the IHL content was quantified by the AMARES algorithm in jMRUI software v5.2.

#### Saliva and buccal swabs

2.2.7

To determine the oral microbiota composition and to measure salivary amylase activity, saliva was collected at baseline and every week during the dietary intervention. Saliva was collected by the passive drool collection method (Salimetrics, Carlsbad, United States). After rinsing their mouth, participants sat in a comfortable position with their heads slightly tilted forward. Saliva was collected by slowly and passively guiding the saliva to the collection tube. Samples were stored at −20°C until further use. Salivary amylase activity was measured using a colorimetric assay (Salimetrics, Carlsbad, United States). Next to the saliva measurements, a buccal swab and/or buffy coat were collected to isolate DNA to measure the copy number variation of genes encoding for salivary and pancreatic amylase: *AMY1, AMY2A,* and *AMY2B* and for future analyses of genetic variation related to glucose and insulin responses. DNA from the buccal swab was isolated using NAOH extraction, and DNA from the buffy coat was isolated using the Blood Mini Kit (Qiagen, Hilden, Germany). Digital droplet polymerase chain reaction (ddPCR) was performed and the copy number of each gene was determined using a reference gene *RPP30* with a known copy number of 2.

#### Intestinal tract measures

2.2.8

Before the start of the dietary intervention and every week during the dietary intervention, faecal samples were collected to measure the faecal microbiota composition. On the day of faecal sample collection, participants were asked to indicate stool frequency of the past week and to rate stool consistency using the Bristol Stool Chart (27). In addition, transit time was measured using the “blue dye method” (28). During the characterization period and at the end of the 9-week dietary intervention, participants consumed two cupcakes containing in total 1.5 g of blue colouring paste (for consumption purposes) within 10 min. The date and time of the first appearance of the blue dye in the faeces were recorded by participants and were used as a measure of transit time.

#### Questionnaires

2.2.9

During the characterization period, participants filled out three questionnaires to assess perceived stress, chronotype, and sleep quality. The Perceived Stress Scale (PSS-10) contained 10 questions about the perceived stress level of participants in the past month (29, 30). The rMEQ (23) was used to assess the chronotype of an individual. In other words, people indicated themselves as a “morning personality type” or an “evening personality type.” Sleep quality over the past month was measured by the Pittsburg Sleep Quality Index (PSQI) (31).

#### Cognitive performance

2.2.10

To examine cognitive performance at baseline, participants performed the Cambridge Neuropsychological Test Automated Battery (CANTAB) consisting of a series of small tests. Before the start of the test battery, participants consumed a standardized meal without caffeine. The tests were performed on a tablet with a touch screen, in a quiet environment to prevent distraction. Participants received a short introduction and underwent a practice round before the start of each test to familiarize themselves with the test. The series of tests took 45–60 min. In total, six tests of the CANTAB gave insight into the performance of three distinct cognitive domains: attention and psychomotor speed, executive function, and memory.

#### Compliance

2.2.11

To increase compliance, participants had to visit the facility twice a week to have a joint dinner under supervision of the researchers and to have the opportunity to ask questions to a research dietician. Two days a week, subsamples of test products were consumed via video calls to monitor compliance. Compliance was optimized by adjusting the restricted eating schedule to an individual’s needs, taking into account regular waking and sleeping times. Furthermore, the free point system enabled participants to choose some products of their preference. Compliance was monitored using the LifeData application (LifeData, Marion, United States) by filling out a short daily questionnaire that asked for any deviations in product consumption, consumption times, and exercise patterns.

### Data management

2.3

Data were collected and stored in an electronic case report form (eCRF) using the data capturing platform Castor EDC (Castor EDC, Amsterdam, Netherlands), which is in accordance with Good Clinical Practice regulations. All protocol deviations and adverse events were recorded via the eCRF.

### Sample size calculation

2.4

We aim to assess whether the glucose response to a meal is sufficiently person-specific to use in personalized dietary advice and will determine person-specific responses to meals and food products in the dietary intervention. The person-specific responses will be identified by correlating the glucose response to a meal or food product to the individual’s average postprandial glucose response over the 9-week controlled diet. An example of potential results is depicted in Figure 3. A high correlation would indicate that individuals are likely to respond as expected based on the average glucose response (Figure 3A), so no person-specific response. Low correlations would indicate a person-specific response; for example, individuals with a high average glucose response may have a low glucose response to the meal or food product, and vice versa (Figure 3B).

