**Methods:**

The question will be assessed under standardized conditions of a 9-week fully controlled dietary intervention in which all meals are the same between individuals and consumed in a fixed order at a fixed time. 63 apparently healthy men and women with a BMI of 25–40 kg/m^2^ and aged 45–75 years were enrolled in the RepEAT study (NCT05456815), of whom 53 participants completed the study. The RepEAT study comprised a fully controlled dietary intervention of nine weeks, consisting of three repetitive periods of three weeks. Within each three-week period, a variety of meals and food products were offered during breakfast, lunch, dinner and in between meal snacks. Throughout the dietary intervention, glucose was continuously monitored using Freestyle Libre Pro IQ monitors. Physical activity was monitored using the ActiGraph and ActivPAL. To measure the association between glucose responses and an individual’s phenotype, various measurements were performed before the start of the dietary intervention including an oral glucose tolerance test, a high-fat mixed meal challenge, assessment of body fat distribution including liver fat (MRI/MRS), and cardiometabolic markers.

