#### 9-week controlled diet

2.1.2

The 9-week diet followed the average dietary pattern of middle-aged men and women in the Netherlands according to the Dutch National Food Consumption Survey 2012–2016. The 9-week diet was designed to maintain a stable body weight, and was not designed to induce any phenotypical changes in an individual. The diet was calculated for eight energy groups ranging from 7–14 MJ / 1,600–3,400 kcal to maintain body weight stability throughout the dietary intervention. The total energy content was adjusted to energy requirements, but was similar in macronutrient composition for all energy groups, i.e., all energy groups received the same energy percentage of each macronutrient.

To design the menu cycle, first the requirements of the diet were specified, including products and meals of interest, restricted time schedules, and portion sizes. These requirements were used in a tailored version of a mixed-integer linear programming model (16) to generate a menu cycle that complied with all constraints. The nutritional composition of the diet was calculated using the Dutch Food Composition Database (NEVO-online version 2021/7.1, RIVM, Bilthoven, Netherlands). The dietary intervention consisted of three repetitive periods of three weeks. Consequently, all food products and meals were given at least three times. Within each three-week period, different versions of the same food product and meal were given at the same eating moment. For instance, participants consumed whole grain wheat bread, refined grain wheat bread, and sourdough bread on the same weekday and the same time of day.

Before the start of the dietary intervention, participants filled out a Food Frequency Questionnaire (FFQ) (17). The results of the FFQ in combination with the Schofield equations (18) were used to estimate a participant’s habitual energy intake and basal metabolic rate, respectively. Based on these calculations, participants were allocated to one of the eight energy groups to maintain body weight stability. To further support weight stability, research dieticians recorded the body weight of participants twice a week. If necessary, participants switched to a higher or lower energy group to remain weight stable.

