#### Food products and meals

2.1.3

To measure the variation in postprandial glucose responses to different food products or meals, we selected a specific set of food products and meals to become incorporated into the controlled diet. These products varied each week in the three-week menu cycle and were selected based on previous literature (4, 6, 8) and societal relevance. For instance, we aimed to assess the variation in glucose responses to whole grain wheat bread, refined grain wheat bread, and sourdough bread. We also aimed to examine the variation in glucose responses to single food products, such as potato chips, chips from potato powder, and popcorn. The food products and meals that were directly compared, were consumed at the same weekday and the same time of day. For all selected products, either the carbohydrate content or the meal size remained similar; for potato chips, chips from potato powder, and popcorn, the carbohydrate content was kept comparable between the products, whereas for the different bread types the number of slices of bread was kept the same.

We also included products that were reformulated to be reduced in sugar content and/or glycaemic index. Within a product category, a reference product and two reformulations were tested within a three-week period, which was copied exactly in the second and third three-week period. Per reference/reformulated product, we once measured plasma glucose and insulin concentrations before and 2 h after consumption. To examine the relationship between consumption of the reformulated foods, glucose response, and perceived well-being, well-being was measured by a questionnaire before and 1, 2, and 4 h after consumption of the reformulated or reference products. Well-being was assessed by the adjusted Multidimensional Mood Questionnaire (MDMQ) (19), asking for fatigue, satisfaction, calmness, energy, the feeling of fitness, and tenseness on a visual analogue scale.

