## Statistical analysis

3

Within the RepEAT study, we aim to examine how replicable glucose responses are within individuals and how consistent the variation in glucose responses is between individuals under standardized conditions of a 9-week fully controlled dietary intervention. To determine the replicability of glucose responses to identical meals and food products within individuals, we will compare the three repetitions per meal or food product. To assess the variability in glucose responses to identical meals between individuals, we will compare the three repetitions per product between individuals. Glucose responses will be corrected for metabolic state of insulin sensitivity by using the average glucose response to all meals in the diet and/or the glucose response to the OGTT, and by correcting for physical activity.

IBM SPSS Statistics and the latest R software will be used to carry out the statistical analyses. Numerical values in descriptive statistics will be reported as mean ± SD, categorical values will be reported as numbers and percentages. To determine the normality of the data, a visual inspection of QQ plots and results of the Kolmogorov–Smirnov test will be used. For linear mixed model analyses, model residuals will be checked for normality. Non-normally distributed data will be transformed before the analyses. *p*-values <0.05 will be considered statistically significant.

Glucose responses to single meals will be measured as the incremental area under the curve (iAUC; mg/dl*hour) and will be calculated from the latest timepoint before consumption until 120 min after consumption. In addition, the glucose peak and time to peak will be measured within each postprandial glucose response curve, within 120 min after consumption of a test product. For each meal and food product there will be three repeated measures during the dietary intervention. Glucose responses to single meals will be associated with the average iAUC of all glucose responses of an individual. There will be adjusted for multiple testing using false-discovery rate adjustment according to the Benjamini-Hochberg procedure (32).

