Up to now, most evidence regarding postprandial glucose responses and variation between and within individuals originates from cohort studies, with only a few standardized meals next to the habitual diet of participants (4, 6, 8). By making use of a fully controlled dietary intervention with continuous glucose and physical activity monitoring, the RepEAT study will provide further insight in the variation in glucose responses independent of external factors such as physical activity, previous meals, and time of day. Moreover, the degree of insulin resistance is an important factor affecting postprandial glucose responses. In the RepEAT study, insulin resistance is determined by an oral glucose tolerance test and will be used to correct for an individual’s insulin resistance status. In addition, all meals were consumed according to a schedule with at least two hours in between meals and snacks to enable us to determine the full glucose response, since on average the glucose concentration returns to baseline within two hours. Furthermore, in order to examine the variation in glucose responses to identical meals and food products within an individual, the 9-week diet consisted of three identical periods of three weeks, resulting in three repetitive measures of postprandial glucose responses to all meals and food products. Given the standardized dietary background, these three repetitive measures per meal and food products will be analysed to measure the robustness of postprandial glucose responses within an individual. Within each three-week period, different versions of the same food product and meal were consumed at the same weekday and time of day, which enables us to study glucose responses to variations of the same food product or meal.

In conclusion, with the RepEAT study we will provide an answer to the question whether person-specific glucose responses to meals are unique and robust enough to be able to be used in personalized advice.

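### Products are judged against an all-meal average while nearly all keep one eating moment, so a personal time-of-day or preceding-meal pattern can look like a person-specific food response

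*Protocol article*

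**What the plan says.** **The index.** Section 2.4 (Sample size calculation) identifies person-specific responses by "correlating the glucose response to a meal or food product to the individual’s average postprandial glucose response over the 9-week controlled diet" and reads a low correlation as person-specific. Section 3 (Statistical analysis) keeps the same reference: "Glucose responses to single meals will be associated with the average iAUC of all glucose responses of an individual". The Introduction's example question asks whether people replicably deviate from their nine-week average after certain foods. The corrections named in section 3 are the all-meal average and/or the OGTT response, and physical activity. Eating moment and preceding meal are not among them.

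**The menu.** The abstract says that "all meals are the same between individuals and consumed in a fixed order at a fixed time". Section 2.1.2 adds that "different versions of the same food product and meal were given at the same eating moment". For the reformulated products, section 2.1.3 describes a three-week set "which was copied exactly in the second and third three-week period". The same section states: "The food products and meals that were directly compared, were consumed at the same weekday and the same time of day".

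**Time of day.** The Introduction reports a higher average response to an identical meal at lunch than at breakfast, and mentions a second-meal effect. Section 2.1.6 says: "Consumption of food products in the evening is associated with a higher glucose response compared to consumption in the morning". The Discussion nevertheless promises insight into "variation in glucose responses independent of external factors such as physical activity, previous meals, and time of day".

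**The concern.** Holding time of day and meal order fixed makes their effects repeat; it does not remove them. Suppose one person tolerates glucose poorly in the evening, relative to their own day. That person will tend to exceed their all-meal average after dinner foods in each of the three cycles. Agreement between the repetitions cannot show whether the food or the eating moment is the cause, because both recur together.

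The trial asks whether responses are person-specific enough to guide dietary advice. A person-by-food effect supports advice on what to eat. A person-by-eating-moment effect supports advice on when to eat. An index with an all-meal reference mixes the two.

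**Working it through.** **The plan's own figures.** The article gives no figure for this point. The only calculation in section 2.4 is the sample size. A two-sided point-biserial test at 0.05 with power 0.80 needs 82 people for r = 0.3 and 44 for r = 0.4, so the two stated numbers reproduce (the text lists them in the other order). Nothing below depends on them.

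**Inputs from the article.** 53 completers; 378 meals over 63 days, so 378/63 = 6 eating moments per day; a 21-day menu; 3 repetitions. Each eating moment then has 63 occasions per person.

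**Inputs that are assumptions.** The variance components, since the article reports none. Person variance is 1, residual (occasion-to-occasion) variance is 1, and person-by-food variance is 0. Person-by-slot variance v is varied.

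**Model.** Response = person + person-by-slot + residual. A slot effect shared by everyone only shifts a product's mean, so it drops out of a correlation across people.

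**Repeat correlation of the deviation from the all-meal average.** The person's average contains 1/6 of each slot effect, so v(1 − 1/6) remains in the deviation:

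ρ = (5/6)v / [(5/6)v + 1]

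**Correlation of a product's three-repeat mean with the all-meal average.**

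r = √[(1 + v/6 + 1/378) / (1 + v + 1/3)]

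| Slot SD (variance v) | ρ, formula | ρ, simulated | r, formula | r, simulated |
|---|---|---|---|---|
| 0 (0) | 0 | 0.00 | 0.87 | 0.86 |
| 0.25 (0.0625) | 0.05 | 0.05 | 0.85 | not run |
| 0.5 (0.25) | 0.17 | 0.17 | 0.81 | 0.81 |
| 0.71 (0.5) | 0.29 | 0.29 | 0.77 | 0.77 |
| 0.75 (0.5625) | 0.32 | 0.31 | 0.76 | not run |
| 1 (1) | 0.45 | 0.45–0.46 | 0.71 | 0.70 |

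**Noisier responses.** With residual variance 4 and v = 0.5 or 1, simulated ρ is 0.09 or 0.16. The correlation r falls from 0.65 (no slot pattern) to 0.61 or 0.59.

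**Can the index tell food from slot?** The simulation was repeated with a true person-by-food variance of 0.5 and no slot pattern.

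| Scenario | r with all-meal average | ρ, all-meal reference | ρ, same-slot reference | ρ, difference of two products in one slot |
|---|---|---|---|---|
| Slot variance 0.5, no food effect | 0.77 | 0.29 | −0.01 | 0.00 |
| Food variance 0.5, no slot effect | 0.74 | 0.33 | 0.31 | 0.33 |

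The all-meal index gives nearly the same answer in both scenarios. The same-slot reference and the within-slot contrast separate them. The near-zero values in the first row follow from the model, because slot is the only interaction in it. Preceding-meal effects were not simulated.

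**The case against.** The case against is substantial, and much of it stands.

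- **Slots are not fixed without exception.** A reader might infer that every meal always sits in the same slot behind the same meals. That is not so. On the time-restricted-eating Saturdays (section 2.1.6) identical meals were eaten in an early window, a late window and the regular schedule, and 5–10% of the diet was self-chosen (section 2.1.2). However, each window was used on one Saturday only, and no stated analysis uses those days to adjust the index.
- **Time of consumption is an object of study.** The Discussion says that person-specific variation will be related to it, and section 2.1.6 plans to relate chronotype to glucose variability. Detailed model terms may also sit in an analysis plan that is not shown. But the reference average is fixed in the article itself, in two sections.
- **The cited effects are average effects.** The lunch-versus-breakfast and evening findings do not establish that people differ in their slot pattern. One can say that such a pattern can pass for a food response, not that it will.
- **The planned correlation moves modestly.** Values of 0.81–0.70 lie in the upper part of the 0.49–0.85 pilot range and well above the expected 0.3–0.4. The article sets no cut-off. A reader might infer that the plan would declare such products person-specific; the documents do not support that. The repeat correlation of deviations answers the Introduction's example question and is a different statistic from the correlation in section 2.4.
- **Direct product comparisons are protected.** They share weekday and time, so a person's slot pattern cancels. The concern does not reach them.

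**Conclusion.** The point holds in limited form. With the all-meal reference, a person-specific eating-moment or preceding-meal pattern can replicate across cycles and lower the product–average correlation without any person-by-food effect. The three repetitions do not rule it out.

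Its size is unknown. For a person-by-slot SD of 0.25 to 1 times the residual SD, the repeat correlation of deviations runs from negligible (0.05) to considerable (0.46). For slot variance 0.25 to 1, the product–average correlation drops from 0.86 to about 0.81–0.70. Both ranges rest on assumed variance components.

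It would be wrong to conclude that the trial cannot identify person-specific food responses, since the same-weekday, same-time contrasts already provide a basis for that. What the design does not deliver is the independence from previous meals and time of day claimed in the Discussion: it observes most products at one time of day and in one meal order.

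**What to change.** 1. Base claims that a response is person-specific to a food on the contrasts between products served on the same weekday and at the same time (section 2.1.3).
2. In sections 2.4 and 3, keep the association with the all-meal average. Report next to it the association with the person's average for the same eating moment, leaving out the tested product. A mixed model with a person-by-eating-moment random effect is an alternative.
3. In the Discussion, replace the claim of independence from previous meals and time of day with a statement that responses were observed at a fixed time of day and meal order.
4. State as a limitation that person-specific second-meal effects are not removed by the slot reference.

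**Cost.** Analysis and wording only; the data exist and were still being cleaned when the article was written. The slot reference is somewhat noisier: about 63 occasions instead of 378, or 60 once the tested product's three are left out. Where one food type dominates a slot, it may also absorb a real person-by-category response. It should therefore be added beside the all-meal average, not put in its place.
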